	**Objectives**
Session 1 (S1): knowledge of the disease	- To identify the cognitive impairment of the patient in everyday life
	- To recognise the remaining functional abilities
	- To determine the nonpharmacological measures to be implemented
Session 2 (S2): pharmacological and nonpharmacological treatments. Behavioural and psychological symptoms of dementia	- To understand the potential effect of pharmacological therapies
	- To identify behavioural and psychological symptoms of the disease
	- To implement nonpharmacological measures to prevent these symptoms
Session 3 (S3): crisis situations. Prevention of caregiver’s exhaustion	- To identify conditions of high risk (treatment modification, concomitant illness, change of environment, relocation)
	- To recognise and prevent caregiver’s burnout
	- To identify their resources
Session 4 (S4): assistive devices and care pathways	- To understand assistive devices, respite and legal aspects raised by the disease
	- To identify the resources available in crisis or emergency situations (general practitioner, specialist consultation, hospitalisation)

THERAD, Therapeutic Education in Alzheimer’s Disease.

Each session is adaptable to the objectives of the participants in each group. The goal we intend to achieve during these group sessions is to develop the caregivers’ coping strategies. It is also part of the educational process to offer them emotional support.

The sessions are led by a geriatrician (S1 and S2) and a nurse (S2, S3 and S4), both trained in therapeutic education, in tandem with stakeholders belonging to the geriatric department: a pharmacist (S2), a psychologist (S3) and a social worker (S4). The pedagogic methods and tools are those currently used in therapeutic educational programmes [40]. We use tools such as storytelling or drawings that allow us to explore the subject’s representations and worries [44]. We also use computer-based activities and brainstorming, as commonly used in health education.

Patients can also receive written documents, when needed, to support the educative process delivered to their relatives during group sessions.

After the group session, the dyads benefit from an individual visit at M2. This is the continuation of the educational process with a reformulation of their personal objectives: ‘achieved’, ‘to reach’, ‘new goals’ and ‘acquired skills’. We try to deliver additional advice based on this evaluation, to both the patient and the caregiver. The patient is interviewed, using the booklet, on his/her well-being.

We are also collecting data regarding the participants’ satisfaction. These qualitative data are part of the educational process.

### Analysis

Data are collected in the Access database and SAS software (developped by the SAS institute based in Cary, North Carolina, USA) will be used to perform the statistical analysis. Intention-to-treat analysis using a linear mixed model will be performed, adjusting for patient (disease severity) and caregiver (burden) characteristics and occurrence of life events that may interfere with the patient’s QoL. Attrition of dyads has been taken into account. At the moment, at the 12-month visit, there is less than 5% attrition. Moreover, the total sample size required for the study was calculated anticipating a risk of 20% attrition to take into account this phenomenon, which is particularly important in our population [45].

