### Secondary outcome measure

The secondary endpoints are: the frequency and severity of the patient’s behavioural and psychological symptoms of dementia assessed by the NeuroPsychiatric Inventory [31]; the patient’s functional autonomy assessed by the Activities of Daily Living scale [32] and the Instrumental Activities of Daily Living scale [33]; the patient’s QoL assessed by the Logsdon QoL-AD scale, self-reported; the primary caregiver’s burden assessed by the Zarit Burden Inventory [34]; the primary caregiver’s QoL assessed by the Nottingham Health Profile [35]; and the primary caregiver’s mood assessed by the mini-Geriatric Depression Scale [36].

We are collecting these data at 2 months, 6 months and 12 months. Lastly, we are collecting information on factors that can influence QoL, as demonstrated in the literature, such as acute disease for both the patient and his/her primary caregiver, change in home care support, hospitalisation or institutionalisation [37].

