Then caregivers benefit from four group sessions, one per week for a month. These sessions are conducted in small groups (six to eight caregivers) and last 3 hours each. They aim towards allowing people to gain better understanding of their relative’s illness, have their concerns addressed and have their feelings expressed. We have planned four group sessions for caregivers, each focusing on a specific aspect of the disease: Session 1 (S1) – knowledge of the disease, understanding of the symptoms, functional abilities; Session 2 (S2) – treatment (pharmacological and nonpharmacological aspects), behavioural and psychological symptoms of dementia in daily living; Session 3 (S3) – management of crisis situations and prevention of caregiver’s exhaustion; and Session 4 (S4) – assistive devices, home care support and care pathways. Table 1 describes the objectives and topics of the group sessions.

**Table 1 T1:** Educational objectives of the group sessions in the intervention group of the THERAD study

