
During the follow-up visits, we check the influence of the intervention on the carer’s perception of QoL by collecting, at each visit, data concerning his/her burden and depression. Indeed, burden and depression have been pointed out to influence the caregiver’s rating of the QoL [22],[49],[50],[52],[53]. We also collect data regarding patient’s cognition, which can also influence the caregiver’s rating of the QoL. The intervention in itself is designed to improve caregivers’ knowledge and to modify their attitude or behaviour, but not to specifically decrease their burden or improve their mood. Furthermore, psychosocial interventions have shown mild to modest efficacy in mitigating caregiver burden in high-quality meta-analyses. Many studies showed improvements in caregiver burden-associated symptoms (for example, mood, coping, self-efficacy) even when caregiver burden itself was minimally improved [57]. We thus hypothesised that the potential effect of our intervention would not be linked to a lesser caregiver’s burden that might modify his/her assessment of the patient’s QoL, but to an improvement in the patient’s QoL itself. There are similar data regarding patient’s depression [58] and cognitive function outcome, on which psychoeducational interventions have not demonstrated any positive impact [1]. Lastly, psychoeducational intervention providing caregiver education can decrease behavioural and psychological symptoms of dementia [13],[59] but these symptoms have not been correlated with the caregiver’s rating of the QoL [60].

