## Conclusion

The THERAD study is the first trial designed to assess the specific impact of a therapeutic educational programme on the AD patient’s QoL. By helping AD patients’ caregivers to develop coping strategies and to increase their knowledge of the disease, we believe that the patient’s QoL could improve. If so, a corollary benefit would appear, such as a reduction in hospitalisations – which are frequent in this population, particularly in emergency departments [65]. The final results of this study may indicate whether such an approach needs to be implemented in the care plan of AD patients.

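### The only efficacy model described adjusts for life events that occur after randomisation, so its treatment coefficient need not be the total effect of assignment

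*Protocol article*

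**What the plan says.** **The model (Analysis).** One analysis is described: "Intention-to-treat analysis using a linear mixed model will be performed". The same sentence then sets out its covariates: "adjusting for patient (disease severity) and caregiver (burden) characteristics and occurrence of life events that may interfere with the patient’s QoL". No time point is attached to any of the three covariates, and no second model without life events is mentioned.

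**The events (Secondary outcome measure).** Directly after giving 2, 6 and 12 months as the collection times for the secondary endpoints, the article says it also records factors that can influence quality of life: "acute disease for both the patient and his/her primary caregiver, change in home care support, hospitalisation or institutionalisation".

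**Links from programme to events.** The group sessions include "Session 4 (S4) – assistive devices, home care support and care pathways" (Intervention). Table 1 adds, for the same session, learning which resources to use in a crisis, hospital among them. The Conclusion says that if quality of life improves, "a corollary benefit would appear, such as a reduction in hospitalisations".

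**Burden.** The secondary endpoints include "the primary caregiver’s burden assessed by the Zarit Burden Inventory". It is measured at M0, before allocation (Detailed study scheme), and again in follow-up: "we check the influence of the intervention on the carer’s perception of QoL by collecting, at each visit, data concerning his/her burden and depression" (Discussion). The Discussion also states that the programme was not designed specifically to reduce burden.

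**The concern.** A covariate can safely be adjusted for in a randomised comparison when it is fixed before allocation. The life events are not. Once an event can depend on the arm, holding it constant changes the question from the effect of being offered the programme to the effect among dyads with the same event history. Two things can go wrong:

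- **Lost effect.** If the programme helps partly by improving home support or avoiding admissions, that part is credited to the event term and not to treatment.
- **Induced bias.** If events and quality of life share an unmeasured cause such as frailty, then at equal event status the two arms no longer have the same frailty. The difference between arms then partly reflects frailty.

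At stake is the meaning of the trial's main estimate. Readers will take an analysis labelled intention-to-treat as the overall benefit of offering the programme, and this coefficient need not be that.

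**Working it through.** **1. Timing of each covariate**

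| Covariate | When it arises | Can assignment change it? |
|---|---|---|
| Disease severity (MMSE) | Measured at M0, before allocation | Not the M0 value |
| Caregiver burden (Zarit) | M0 and every later visit; the model does not say which | Not the M0 value; later values could change |
| Life events | Listed beside the 2-, 6- and 12-month data; patients are community-dwelling at entry, so institutionalisation can only come later | Yes for home support (Session 4); hospital stays anticipated to fall if quality of life rises |

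Only the life events are post-randomisation by their nature.

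**2. The plan's own figure**

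Inputs from Sample size: SD 5.5; difference 5% of 52 = 2.6 points; alpha 5% (two-sided assumed); power 80%; attrition 20%.

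- n = 2 × [5.5 × (1.960 + 0.842) / 2.6]² = 70.25 per arm.
- 70.25 × 1.2 = 84.3, rounded up to 85. The stated 85 per arm is reproduced.
- Completers: 85 × 0.8 = 68 per arm. Standard error = 5.5 × √(2/68) = 0.943.
- Power = Φ(2.6/0.943 − 1.96) = 78.7%. This is the reference value below.

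**3. Illustration: part of the effect runs through the events**

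The share m is an assumption; the article gives none. Adjusted coefficient = 2.6 × (1 − m). Power uses 68 per arm and SD 5.5, ignoring any fall in residual SD from adjustment.

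| m | Adjusted coefficient | Power |
|---|---|---|
| 0 | 2.60 | 78.7% |
| 10% | 2.34 | 70% |
| 20% | 2.08 | 60% |
| 30% | 1.82 | 49% |
| 40% | 1.56 | 38% |

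**4. The same, by event rates**

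Amount removed = points lost per event × difference in event risk between arms. Rates and costs are assumptions.

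- 20% against 10%, 2 to 4 points per event: 0.10 × 2 = 0.2 to 0.10 × 4 = 0.4 removed; coefficient 2.4 to 2.2; power 72% to 65%.
- 30% against 15%, 2 to 4 points: 0.15 × 2 = 0.3 to 0.15 × 4 = 0.6 removed; coefficient 2.3 to 2.0; power 68% to 56%.
- 20% in both arms: nothing removed; coefficient 2.6.

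These rates correspond to m of 0.2/2.6 = 8% up to 0.6/2.6 = 23%, so the upper rows of the table in step 3 need stronger assumptions still.

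**5. Illustration: shared unmeasured cause**

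Two million dyads were simulated with no treatment effect on quality of life. An unmeasured standard normal health variable U raises quality of life by 3 points per SD (added noise SD 4.6, total SD about 5.5). The log-odds of an event is −1.2 − U − b × treatment.

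| b | Event risk, control vs programme | Unadjusted difference | Event-adjusted difference |
|---|---|---|---|
| 0 | 27% vs 27% | 0.00 | 0.00 |
| 0.5 | 27% vs 19% | −0.01 | −0.20 |
| 1.0 | 27% vs 13% | 0.00 | −0.35 |

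The unadjusted comparison is right throughout. The adjusted one shows a false harm that grows with the programme's effect on events. If the programme made an event more common, as it might for a change in home support, the sign would reverse.

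**The case against.** **The window is short.** The primary endpoint is at 2 months. The sessions run weekly for one month, and those on crises and home support come last. There may be little time for event rates to separate by then. This stands and argues for a small bias at M2. It does not make the covariate safe, since a change in home support is plausible within weeks.

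**Not every event is a target.** No session aims to prevent acute illness in patient or caregiver; concomitant illness appears in Table 1 only as a risk to recognise. This also stands. The point rests on home support and hospital stays. The statement about hospital stays is conditional on better quality of life, so the path there runs from outcome to event. That is no defence: conditioning on a consequence of the outcome can also distort the treatment coefficient.

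**A condensed article leaves covariate detail to the analysis plan.** That is fair for the timing of severity and burden. It does not cover life events, which the article itself places in the model.

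**Stronger readings that a reader might infer.** One is that the analysis is not intention-to-treat, or cannot be interpreted. The text does not show this: nothing in Analysis departs from analysing dyads as randomised, and the coefficient has a meaning, though not necessarily that of a total effect. Another is that the model adjusts away burden, which the programme is meant to lower. The Discussion says lowering burden was not a specific aim, and the feasibility study found no significant change in it. Session 3's objective on caregiver burnout shows only that burden could change. Burden listed as a caregiver characteristic reads naturally as the M0 Zarit score, a valid covariate.

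**Conclusion.** The point holds for life events. As written, the only efficacy model described conditions the treatment effect on variables that arise after randomisation, and the article gives reason to think that the programme may affect at least two of them. The coefficient need not be the total effect of assignment.

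The size cannot be derived from the article. Under an assumed 10–40% share running through the events, the planned 2.6 points would be estimated as 2.34–1.56. Under the assumed event rates the estimate would be 2.4–2.0. With a shared cause and no true effect on quality of life, the false difference was −0.20 to −0.35 points. In all three illustrations the bias is zero if the programme leaves event rates unchanged, and the 2-month window makes a large shift less likely. The case for changing the model is therefore that the adjustment risks bias that is easily avoided, not that a large bias is documented.

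For burden no error is shown; only the time point needs confirming.

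**What to change.** - **Primary model.** Remove life events. Limit covariates to values measured at M0 before allocation: caregiver-rated QoL-AD (unless baseline already enters as one of the repeated outcomes), MMSE and Zarit score. State explicitly that severity and burden are the M0 values.
- **Life events.** Report them by arm. Use them, or follow-up burden, only in an analysis labelled as sensitivity or exploratory mediation, with its assumptions stated.
- **Cost.** One or two sentences of analysis wording, best settled before database lock. All these baseline measures are already collected at M0, so no new data are needed, and the stated sample size does not change. Making hospitalisation or institutionalisation formal secondary outcomes would be a design preference and is not needed to correct this point.

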## Discussion

The THERAD study started in January 2013. To date, 107 dyads have been included. The final results will be available in 2015. By transmitting knowledge, expertise and skills to the AD patient’s caregiver [46], we hypothesised that the patient’s QoL can improve. QoL assessment provides a format to express whether an intervention has made an important difference to the patient’s life, but its measurement is a challenge in AD [20],[21],[28],[47]. Indeed, the abstract nature of QoL limits its use to individuals who have the cognitive capacity to understand the concept, a capacity that is gradually lost in neurodegenerative diseases such as AD (for example, the comprehension of the item ‘you as a whole’ or ‘you in general’) [21]. For this reason, self-rating of the QoL is often replaced by proxy rating. However, it has been shown that there could be differences on QoL ratings between patients, caregivers and theoretical models [48]. Caregivers consistently rate the patient’s QoL lower [14],[49], not only because of cognitive function [22],[50],[51] but also because of the caregiver’s burden or depression [22],[49],[50],[52],[53] and the patient’s depressive symptoms [54]. Acknowledging the problem of potential bias of proxy reports, we chose a proxy rating for QoL in the THERAD study, for several reasons. Firstly, it has been demonstrated with increasing severity of the disease that patient ratings must mostly be replaced by proxy ratings [55],[56], even if Logsdon and colleagues showed in 2002 that patients can rate their own QoL until the late stages [28]. This last study showed that the correlation between caregiver’s rating and patient’s rating was greatest for subjects in the middle tertile of cognitive function, and the recruitment of our centre for the THERAD study is mainly moderately affected patients. Then in our routine practice we found that it was difficult to estimate the patient’s QoL with self-rating. First, the patient’s ability to identify changes or to make choices among options in a scale is affected by lack of insight, due to anosognosia [30],[54]. Moreover, cognitive impairment, with varying deficits of memory, attention, judgement, insight and communication, influences the ability of individuals to comprehend questions or make comparisons in complex domains [47]. Then, at the moderately severe stage of the disease, patients must receive important help from the rater to complete the scale, which can introduce a real bias – the experimenter’s bias. For all these reasons we chose to use the caregiver’s rating of the AD patient’s QoL. We also decided to add self-rating methods as a secondary outcome in the THERAD study, because it has been demonstrated that self-rating and caregiver’s ratings are complementary and should be treated separately [20].

During the follow-up visits, we check the influence of the intervention on the carer’s perception of QoL by collecting, at each visit, data concerning his/her burden and depression. Indeed, burden and depression have been pointed out to influence the caregiver’s rating of the QoL [22],[49],[50],[52],[53]. We also collect data regarding patient’s cognition, which can also influence the caregiver’s rating of the QoL. The intervention in itself is designed to improve caregivers’ knowledge and to modify their attitude or behaviour, but not to specifically decrease their burden or improve their mood. Furthermore, psychosocial interventions have shown mild to modest efficacy in mitigating caregiver burden in high-quality meta-analyses. Many studies showed improvements in caregiver burden-associated symptoms (for example, mood, coping, self-efficacy) even when caregiver burden itself was minimally improved [57]. We thus hypothesised that the potential effect of our intervention would not be linked to a lesser caregiver’s burden that might modify his/her assessment of the patient’s QoL, but to an improvement in the patient’s QoL itself. There are similar data regarding patient’s depression [58] and cognitive function outcome, on which psychoeducational interventions have not demonstrated any positive impact [1]. Lastly, psychoeducational intervention providing caregiver education can decrease behavioural and psychological symptoms of dementia [13],[59] but these symptoms have not been correlated with the caregiver’s rating of the QoL [60].

The THERAD study follows a feasibility study we conducted at Toulouse University Hospital between January 2010 and January 2011. This was a 12-month monocentric quasi-experimental before and after study. The inclusion criteria were the same as those of the THERAD study. The main outcome was the patient’s QoL as assessed by the caregiver. Our secondary outcomes were: patient’s functional autonomy assessed by the Activities of Daily Living and the caregiver’s burden assessed by the Zarit Burden Interview. Twenty-nine dyads of AD patient/caregiver were included. At 2 months there was a significant increase in the patient’s QoL (24.6 ± 5.1 at M0 vs. 27.2 ± 6.0 at M2, *P* = 0.038). This was an encouraging result and the first step in the development of the THERAD study. Of course, this study had limitations, mainly its lack of statistical power. Use of the caregiver’s rating of the AD patients QoL can also be considered a limitation, in a combined intervention programme, but this limitation appears to be minimal. Indeed the educational programme was not specifically designed to improve the caregivers’ burden or depression, factors that have been pointed out to influence caregiver’s perception of the patient’s QoL. However, acknowledging this problem of proxy rating, we chose to add self-rating methods as a secondary outcome in the THERAD study. Moreover, it has been demonstrated that self-rating and caregiver’s ratings are complementary and should be treated separately [20]. This improvement in patients’ QoL was in accordance with the evidence from the literature. As mentioned earlier, a systematic review has shown that multidimensional approaches including, but not involving only, therapeutic education, caregiver support and respite improve the patient’s QoL [23]. In addition, it has been shown that therapeutic educational programmes can improve patients’ QoL in many chronic diseases [61],[62].

However, our feasibility study showed no significant differences in patients’ functional autonomy or caregivers’ burden over time. This is also consistent with the results in the literature. Indeed, the randomised controlled AIDMA study (psycho-educational programme assistance to caregivers of Alzheimer’s patients) [3] has not demonstrated any positive result on the patient’s functional independence measured by the Disability Assessment for Dementia [63]. In our opinion, an improvement in functional autonomy did not constitute an appropriate primary outcome measure for this type of intervention, in the light of the disease’s evolution. This study has, by contrast, shown an increased ‘sense of competence’ of the caregiver measured by the Sense of Competence Questionnaire [64]. Given the evidence from the literature and our daily experience, we hypothesise in the THERAD study that therapeutic education of both primary caregivers and AD patients could improve the AD patient’s QoL. If the efficacy of this type of approach is proven, and persists in the year after inclusion, then it will be important to implement such programmes in the care plan of AD patients.

